## Abstract

Importance: Although prolonged fasting has become increasingly popular, the favourable biological adaptations and possible adverse effects in humans have yet to be fully elucidated. Objective: To investigate the effects of a three-day water-only fasting, with or without exercise-induced glycogen depletion, on autophagy activation and the molecular pathways involved in cellular damage accumulation and repair in healthy humans. Design: A randomised, single-centre, two-period, two-sequence crossover trial. The primary outcome is autophagic activity, assessed as flux in peripheral blood mononuclear cells (PBMCs) measured in the context of whole blood. Secondary outcomes include changes in body composition, heart rate variability, endothelial function, and genomic, epigenomic, metabolomic, proteomic, and metagenomic adaptations to fasting in plasma, platelets, urine, stools, and PBMCs. Detailed profiling of circulating immune cell populations and their functional states will be assessed by flow cytometry. Setting: All clinical investigations will be undertaken at the Charles Perkins Centre Royal Prince Alfred Hospital clinic, University of Sydney, Australia. Participants: Twenty-four individuals aged 18 to 70 years, with a BMI of 20–40 kg/m^2^, free of major health conditions other than obesity. Discussion: While autophagic flux induction through fasting has garnered interest, there is a notable lack of human studies on this topic. This trial aims to provide the most detailed and integrated analysis of how three days of prolonged water-only fasting, combined with glycogen-depleting exercise, affects autophagy activation and other crucial metabolic and molecular pathways linked to cellular, metabolic, and immune health. Insights from this study may pave the way for safe and effective strategies to induce autophagy, offering potential preventive interventions for a range of chronic conditions.

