## 3. Methods

### 3.1. Study Design

The PROFASTA trial is a randomised, single-centre, two-period, two-sequence crossover study, involving a total sample of 25 participants. Participants will be randomly assigned into two groups, with each group undergoing two different interventions in separate phases (Figure 1). By the study’s end, all participants will have completed both Intervention A and Intervention B, ensuring robust within-subject comparisons to strengthen the validity of the findings. Intervention A consists of a three-day water-only fast, while Intervention B includes a three-day water-only fast that is preceded by a single session of glycogen-depleting endurance exercise conducted on the first day of the fasting period, following an overnight fast. Detailed clinical visits and procedures are outlined in Table 1 and Table 2. This study has been approved by the Sydney Local Health District Ethics Committee (2022/ETH00617), and all study visits will take place at the Charles Perkins Centre-Royal Prince Alfred Hospital (CPC-RPA) clinic. The protocol has been prepared using the SPIRIT reporting guidelines [26].

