### 3.5. Randomisation

Participants will be randomly assigned using a web-based system in REDCap, employing random permuted blocks with a block size of four. Randomisation will occur at the beginning of visit 3, after all baseline measurements have been completed (Figure 1, Table 1). The study coordinator will disclose group assignments to both the study team and the participant upon their arrival for the clinic visit #3. While blinding participants and investigators is not feasible due to the nature of the intervention, those conducting sample analysis and statistical analysis will remain blinded to group allocations, when possible.

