### 5.5. Sample Size Calculation

A total of 25 volunteers will be recruited for the study. Given the crossover design, each participant will undergo both interventions, effectively creating two groups of 25. To estimate the required sample size, the change in LC3B-II to beta-actin ratio was considered. LC3B-II, the lipidated form of microtubule associated protein 1 light chain 3 beta that accumulates on autophagosomes when lysosomal degradation is blocked, is the gold standard marker for measuring autophagic flux in human samples [30]. Utilising ANOVA with a repeated measures design, assuming a standard deviation of 95.4, and aiming for 80% power at a significance level of 0.05, a difference of 30% (a change of 134.7 from a mean of 299.3 ng/mg protein/hour in the control group at baseline) could be detected with a sample size of 20 per group. Accounting for an estimated dropout rate of 20%, the initial recruitment target is set at 25 participants, based on the study by Bensalem et al. [29]. Sample size versus power plot is shown in Supplementary Figure S1. Additionally, sensitivity analyses, examining sample size requirements for detecting 20% and 40% changes, are shown. The exploratory outcomes will not be separately powered but will provide valuable hypothesis-generating data for future targeted studies.

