## Figures and Tables

**Figure 1 nutrients-16-04297-f001:**
[figure not shown]
Experimental Design of the PROFASTA Trial. This randomised, two-period, two-sequence crossover trial involves 20 participants who are assigned to two interventions: Intervention A consists of a 3-day water-only fast, while Intervention B involves a 3-day water-only fast preceded by a single bout of glycogen-depleting endurance exercise performed on the first day of fasting. Each participant will complete both interventions, allowing for a comprehensive assessment of the effects of fasting and exercise on autophagic flux and other metabolic adaptations.

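### The planned sample size is given as 24, 25 and 20 in different places, and only 25 agrees with the plan's own requirement of 20 per group after 20% dropout

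*Protocol article*

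**What the plan says.** Four places give a number of participants.

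- Abstract: "Twenty-four individuals aged 18 to 70 years".
- Section 3.1 (Study Design): "involving a total sample of 25 participants". The next sentence there has the participants randomised into two groups.
- Section 5.5 (Sample Size Calculation): "A total of 25 volunteers will be recruited for the study". It then says that the target difference "could be detected with a sample size of 20 per group", allows for 20% dropout, and concludes that "the initial recruitment target is set at 25 participants". Because each person receives both interventions, the section counts this as two groups of 25.
- Figure 1 caption: the "crossover trial involves 20 participants who are assigned to two interventions".

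No place explains the 24, and the caption does not describe its 20 as completers.

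**The concern.** The three numbers cannot all be the planned total. They are not plainly three stages of one flow (for example 25 recruited, 24 randomised, 20 completing). Section 3.1 calls 25 the total sample and moves straight to randomisation, while the caption describes its 20 as assigned.

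The number matters because the power statement rests on 20 people contributing both periods. The allowance for loss has work to do here. Under section 4.2, participants who cannot reach the minimum exercise dose are withdrawn from that arm, and under section 3.5 randomisation has already taken place by then. In a crossover such a loss removes the within-person comparison. A reader of the Abstract or the figure alone would take away a target that falls short of the one derived in section 5.5.

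**Working it through.** **Inputs.** From section 5.5: 20 needed per group; dropout 20%; SD 95.4; control mean 299.3; difference stated both as 30% and as 134.7; power 80%; significance level 0.05 (taken as two-sided, which the section does not say). Totals: 24 (Abstract), 25 (3.1 and 5.5), 20 (Figure 1).

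**Step 1: reproduce the plan's target.** N = n/(1 - dropout) = 20/(1 - 0.20) = 25. The derivation in section 5.5 is correct.

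**Step 2: expected completers for each stated total,** N x (1 - 0.20), and the largest dropout that still leaves 20, 1 - 20/N:

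| Stated total | Expected completers | Largest dropout leaving 20 |
|---|---|---|
| 25 | 20.0 | 20% |
| 24 | 19.2 | 16.7% |
| 20 | 16.0 | 0% |

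Only 25 meets the requirement at the stated dropout.

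**Step 3: where 24 might come from.** 20 x 1.2 = 24, which is a common slip in allowing for dropout. Also 6 x 4 = 24, six full blocks of the size given in section 3.5. The article states neither origin, so this remains a guess.

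**Step 4: which difference goes with 20 per group.**

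- 30% of 299.3 is 89.8. With SD 95.4 the standardised difference is 89.8/95.4 = 0.94. An unpaired two-sample t test then needs 19 per group. A paired t test with correlation 0 (SD of the difference 95.4 x √2 = 134.9) needs 20.
- 134.7 is 134.7/299.3 = 45.0% of the mean. It needs 9 per group with a two-sample t test, or 7 to 10 people with a paired t test as the correlation falls from 0.5 to 0.

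So the 20 reproduces with 89.8 and not with 134.7. That conflict is a separate matter, but it limits what can be said about power here.

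**Step 5: power at the resulting completer counts.** The correlations are assumptions, as the article gives none.

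| Completers | 89.8, two-sample t | 89.8, paired t, correlation 0 | 89.8, paired t, correlation 0.5 | 134.7, two-sample t |
|---|---|---|---|---|
| 20 | 0.83 | 0.81 | 0.98 | 0.99 |
| 19 | 0.81 | 0.78 | 0.97 | 0.99 |
| 16 | 0.73 | 0.70 | 0.94 | 0.97 |

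The completer counts in step 2 follow directly from the document. The power values depend on choices that it leaves open.

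**The case against.** The strongest reply is that this is editorial. The two sections that govern the design agree on 25 and the dropout arithmetic is right. The outliers are one line of an abstract and one caption. The gap between 24 and 25 is 0.8 of an expected completer, about two points of power in the unpaired calculation. All of that stands, and it sets the severity.

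Four stronger readings are tempting and should be resisted.

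- *That the trial is underpowered.* This is not shown. Power falls below 80% at 16 completers only if the 20 in Figure 1 means people randomised, if 20% of them are then lost, if the difference is 89.8, and if pairing earns little or no credit. Section 5.5 names a repeated-measures analysis and also states a difference of 134.7. With that difference, power at 16 is 0.97 in the unpaired test.
- *That Figure 1's 20 is simply the number of completers.* This is plausible, since it matches the 20 in section 5.5, and if so only the label is wrong. But the caption calls them assigned, so it is an inference.
- *That 25 clashes with "random permuted blocks with a block size of four".* It does not. Permuted blocks do not require a total divisible by four, and nothing in the article promises equal sequences. With a single list, six full blocks give 12:12 and the 25th person makes it 13:12, which is harmless in a crossover.
- *That three totals would let the target be chosen after the fact.* This is speculation. Section 5.5 fixes a recruitment target of 25.

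**Conclusion.** The inconsistency is certain: the current text gives 24, 25 and 20, and only 25 agrees with the derivation in section 5.5. At the stated 20% dropout the other two fall short of 20 completers by 0.8 (24) and 4.0 (20). It should be corrected, but it does not threaten the design.

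The shortfalls apply the 20% to whichever total is stated. Section 5.5 speaks of people recruited and does not say how much of the loss falls before randomisation at visit 3.

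The effect on power cannot be settled until section 5.5 resolves the difference (89.8 or 134.7), the type of SD and the within-person correlation. For 89.8 without credit for pairing it is about 0.78 to 0.81 at 19 and 0.70 to 0.73 at 16. Positive correlation would raise these values.

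**What to change.** State one target throughout.

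- Change the Abstract from 24 to 25.
- Change the Figure 1 caption to 25 or, if the 20 is meant as those expected to complete both periods, say so there.
- If 24 is in fact the target, change sections 3.1 and 5.5 instead, restate expected completers as about 19, and give the power that goes with 19 on a stated difference, SD and correlation.

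The first two changes cost a few words and add no participants. The alternative also needs the power statement in section 5.5 rerun.

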## 1. Introduction

Prolonged fasting, defined as extended abstinence from calorie intake, lasting longer than 36 or 48 h, has deep roots in religious and cultural traditions across many faiths, including Hinduism, Buddhism, Judaism, Islam, and Christianity [1]. Despite its ancient origins, the first detailed scientific investigations into the physiological effects of prolonged fasting in humans were conducted in the 1960s and 1970s by Cahill and colleagues, long before the advent of molecular biology [2,3,4,5]. Their work demonstrated that fasting triggers profound metabolic adaptations aimed at conserving energy and feeding essential organs with ketones, while minimising the breakdown of muscle protein, enabling survival on minimal resources for extended periods [3]. Remarkably, they found that a person of average weight could survive up to two months on water alone, whereas individuals with obesity are capable of fasting for much longer [6]. One extraordinary case involved a 207 kg man who fasted for 382 days, consuming only calorie-free fluids, vitamins, and minerals, resulting in a dramatic weight loss of 126 kg or 61% of his initial body weight [7].

In recent years, periodic prolonged fasting has gained renewed attention due to claims that it promotes longevity and improves health by influencing cellular ageing and reducing disease risk factors. However, despite its growing popularity, the precise molecular and cellular adaptations and potential risks associated with fasting in humans remain poorly understood [8,9]. For example, one of the key mechanisms linked to fasting’s benefits is autophagy, a tightly regulated process responsible for degrading and recycling damaged organelles and misfolded proteins, thus maintaining cellular homeostasis with ageing [10]. While evidence from animal models supports fasting-induced autophagy, human studies have largely relied on indirect and imprecise markers, such as protein or mRNA levels, as indicators of autophagic activity [11]. The precise dynamics of autophagic flux—the rate at which autophagosomes sequester and degrade cellular components—remain largely underexplored in humans during prolonged fasting. A key barrier to understanding human autophagy has been the reliance on cell culture methods that disrupt the natural nutritional and endocrine signalling present in blood. By maintaining cells in whole blood, which is physiologically intact during flux measurement, we aim to capture how autophagic flux responds to interventions like fasting while preserving the genetic, nutritional, and hormonal factors unique to each individual [12].

Other critical questions remain regarding fasting, including the optimal duration needed to trigger autophagy and whether exercise-induced glycogen depletion accelerates and potentiates this process, given glycogen’s role as the main glucose storage form in the human body. Moreover, while it is well established that prolonged fasting—unlike chronic caloric restriction—reduces circulating IGF-1 levels in humans [13,14,15,16], the effects of prolonged fasting on pathways such as insulin/IGF1/mTOR, which are crucial for DNA repair, cell proliferation, cancer suppression, and ageing, have not been thoroughly investigated in human studies [8,17,18,19]. Further research is essential to clarify how fasting activates cellular processes such as antioxidant defences, DNA repair, proteostasis, mitophagy, and cellular senescence inhibition, as well as its effects on telomere attrition and the modification of DNA methylation and proteomic ageing clocks in healthy individuals [20,21,22,23,24]. A deeper understanding of these mechanisms is crucial for translating the benefits of fasting into safe, therapeutic interventions grounded in well-defined biological pathways. The recent advancements in multi-omic technologies—including genomics, transcriptomics, epigenomics, proteomics, metabolomics, and microbiome metagenomics—offer an unprecedented opportunity to investigate the complex, multi-layered biological processes activated during fasting. These technologies enable the comprehensive profiling of molecular changes across various biological systems, allowing for the integration of data from different omics layers to reveal insights into metabolic regulation, autophagy, immune modulation, and cellular stress responses [25]. This systems-level approach can uncover intricate interactions that were previously inaccessible, potentially leading to the development of more targeted and personalised therapeutic strategies based on fasting-induced molecular alterations.

## 2. Aims of Profasta Trial

The primary aim of the PROFASTA trial is to evaluate the impact of a three-day water-only fast, with and without a single session of glycogen-depleting exercise, on autophagic flux in isolated peripheral blood mononuclear cells (PBMCs) where flux is measured by the introduction of a lysosomal inhibitor into whole blood. The primary hypothesis is that glycogen depletion through exercise prior to fasting will significantly enhance autophagic activation in PBMCs. Secondary objectives include assessing changes in body composition, heart rate variability, endothelial function (measured via flow-mediated vasodilation), as well as plasma metabolomic and proteomic shifts, and microbiome metagenomic adaptations in stool samples.

## 3. Methods

### 3.1. Study Design

The PROFASTA trial is a randomised, single-centre, two-period, two-sequence crossover study, involving a total sample of 25 participants. Participants will be randomly assigned into two groups, with each group undergoing two different interventions in separate phases (Figure 1). By the study’s end, all participants will have completed both Intervention A and Intervention B, ensuring robust within-subject comparisons to strengthen the validity of the findings. Intervention A consists of a three-day water-only fast, while Intervention B includes a three-day water-only fast that is preceded by a single session of glycogen-depleting endurance exercise conducted on the first day of the fasting period, following an overnight fast. Detailed clinical visits and procedures are outlined in Table 1 and Table 2. This study has been approved by the Sydney Local Health District Ethics Committee (2022/ETH00617), and all study visits will take place at the Charles Perkins Centre-Royal Prince Alfred Hospital (CPC-RPA) clinic. The protocol has been prepared using the SPIRIT reporting guidelines [26].

### 3.2. Eligibility Criteria

Participants must meet the following criteria: (1) healthy males and females without disabilities that may hinder cycling exercise participation; (2) aged between 18 and 70 years old; (3) with a BMI within the range of 20–40 kg/m^2^; (4) able to adhere to all study assessments and procedures, including exercise and fasting interventions. Participants will be excluded based on the following conditions: (1) pregnant, breastfeeding, or of childbearing potential and unwilling to implement contraception during the study; (2) a history of chronic diseases that could impede exercise tests or compromise result interpretation; (3) the presence of comorbidities including hypertension, diabetes mellitus, or known cardiovascular disease; (4) a history of supplement or medication use that may affect result interpretation; (5) health conditions, dietary requirements, or psychosocial factors that may interfere with study participation and compliance; (6) unintentional weight loss exceeding 10% of body weight in the past 5 years, as well as smoking, psychiatric, or behavioural issues (e.g., a history of drug/alcohol abuse or eating disorders); and (7) the inability to perform cycling exercises, evidenced by an inability to complete the incremental peak power test during the baseline assessment or the 90 min glycogen-depleting exercise at the beginning of the fasting intervention (Table 3).

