### 3.7. Intervention

After completing the baseline assessments, participants will be randomly assigned to one of two groups: (1) Group 1 will undergo a prolonged water-only fast (Intervention A), while Group 2 will engage in a prolonged water-only fast accompanied by a single session of glycogen-lowering endurance exercise (Intervention B) during phase 1. Following this phase and a 4-week washout period, the groups will switch interventions in phase 2, with Group 1 undergoing Intervention B and Group 2 undergoing Intervention A. For a graphical representation of the experimental design, refer to Figure 1 and Figure 2.

**Table 3 nutrients-16-04297-t003:** Eligibility Criteria for the PROFASTA Trial.

Inclusion Criteria	Exclusion Criteria
• Healthy males and females without disabilities affecting cycling ability	• Pregnancy, breastfeeding, or unwillingness to use contraception if of childbearing potential
• Age 18–70 years	• History of chronic diseases affecting exercise capacity or result interpretation
• BMI 20–40 kg/m^2^	• Presence of comorbidities (hypertension, diabetes, cardiovascular disease)
• Ability to comply with all study procedures and assessments	• Current use of supplements or medications that may affect results
	• Health conditions, dietary requirements, or psychosocial factors affecting compliance
	• Unintentional weight loss >10% of body weight in past 5 years
	• Current smoking, psychiatric conditions, or history of substance abuse/eating disorders
	• Inability to complete baseline exercise tests (incremental peak power test or 90-min glycogen-depleting exercise)

Note: All criteria must be met for study participation. BMI, body mass index.

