### 4.2. Exercise-Induced Glycogen Depletion (80–90 Min)

The exercise protocol, adapted from seminal glycogen depletion studies [27,28], will take place after participants arrive for the start of the fasting visit following an overnight fast and after all initial assessments are complete. Power outputs for the cycle ergometer will be determined based on the incremental VO_2_peak test performed during the screening visit. Participants will engage in 60 min of cycling at a constant power output corresponding to 60–70% of their peak VO_2_, maintaining a cadence of 60–70 rpm, which is classified as moderate-intensity physical activity. After a 5 min rest, the participants will perform repeated 1 min sprints at 90 rpm and 90–100% of their VO_2_peak equivalent power output, with 1 min rest intervals between sprints. The exercise session will conclude after ten sprints or if participants cannot maintain a pedalling rate of ≥80–90 rpm for 1 min. Verbal encouragement will be provided throughout the session, during which heart rates will be recorded using Polar H10 chest strap heart rate monitors. Throughout the exercise session, participants’ fatigue levels will be monitored using the Rating of Perceived Exertion (6–20 RPE) scale, with heart rate and RPE recorded every 10 min during steady-state cycling and after each sprint. The exercise will be terminated if participants report severe fatigue (RPE ≥ 19), experience any adverse symptoms (dizziness, nausea, unusual shortness of breath), or if heart rate exceeds 95% of age-predicted maximum for more than 3 min. If a participant cannot complete the full protocol, a minimum of 60 min of steady-state cycling plus three sprints will be considered sufficient for partial glycogen depletion, allowing continued participation in the study. Those unable to meet these minimum requirements will be withdrawn from this arm of the trial.

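### Completing the exercise bout that defines Intervention B is used as an eligibility criterion although it can only be judged after randomisation, and the article gives two conflicting completion rules

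*Protocol article*

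**What the plan says.** All references are to the protocol article.

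- **What the bout is.** Section 3.1: "Intervention B includes a three-day water-only fast that is preceded by a single session of glycogen-depleting endurance exercise". Intervention A is the fast alone. The same section says every participant will have completed both interventions by the end of the study.
- **When randomisation happens.** Section 3.5: "Randomisation will occur at the beginning of visit 3, after all baseline measurements have been completed".
- **When the bout happens.** Section 4.2 says that it "will take place after participants arrive for the start of the fasting visit following an overnight fast and after all initial assessments are complete". Section 3.7 gives the phase 2 switch as "with Group 1 undergoing Intervention B and Group 2 undergoing Intervention A". The bout therefore falls at visit 3 for Group 2 (B then A) and at visit 7 for Group 1 (A then B).
- **Eligibility.** Section 3.2, exclusion (7), covers inability to complete the peak power test "or the 90 min glycogen-depleting exercise at the beginning of the fasting intervention". Table 3 words it as "Inability to complete baseline exercise tests (incremental peak power test or 90-min glycogen-depleting exercise" and notes that all criteria must be met.
- **Completion during the trial.** Section 4.2 makes an allowance for those who fall short of the whole session: "a minimum of 60 min of steady-state cycling plus three sprints will be considered sufficient for partial glycogen depletion, allowing continued participation". It then adds: "Those unable to meet these minimum requirements will be withdrawn from this arm of the trial".
- **Schedule.** Table 2 ticks inclusion/exclusion at visit 2 only, and exercise at visits 1, 3 and 7. Table 1 shows that the visit 1 exercise is the VO2peak test.

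**The concern.** An eligibility criterion has to be assessable before allocation. This one is not: no run of the glycogen-depleting bout is scheduled before randomisation, so calling it a baseline test in Table 3 does not match the visit schedule. In effect it is a rule for removing randomised participants because of how they performed on one of the two interventions being compared.

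The primary hypothesis is the B-versus-A contrast. If people leave because they could not do B, the contrast no longer describes everyone randomised. The timing of removal also differs by sequence, so the pattern of missing data differs too. Separately, Section 3.2 and Table 3 on one side and Section 4.2 on the other can give opposite answers for the same participant.

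**Working it through.** **Step 1. Timing.** The sources are Sections 3.5, 3.7 and 4.2 and Table 2.

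| Event | Group 1 (A then B) | Group 2 (B then A) |
|---|---|---|
| Inclusion/exclusion ticked | Visit 2 | Visit 2 |
| Randomisation | Start of visit 3 | Start of visit 3 |
| First glycogen-depleting bout | Visit 7 | Visit 3, after randomisation |
| Post-fast data held if removed at the bout | Intervention A, visits 4 and 5 | None |

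The criterion cannot be applied at visit 2 in either group. In Group 1 it can be applied only after the whole of phase 1.

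**Step 2. Session length from the components in Section 4.2.** These are 60 min of steady cycling, 5 min of rest, then 1 min sprints separated by 1 min rests. The ranges depend on whether a rest is counted after the last sprint.

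- Full session, ten sprints: 60 + 5 + 10 + 9 = 84 min, or 60 + 5 + 10 + 10 = 85 min.
- Nine sprints: 60 + 5 + 9 + 8 = 82 min, or 60 + 5 + 9 + 9 = 83 min.
- Minimum, three sprints: 60 + 5 + 3 + 2 = 70 min, or 60 + 5 + 3 + 3 = 71 min.

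The full session fits the 80–90 min in the Section 4.2 heading but is shorter than the 90 min in Section 3.2 and Table 3.

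**Step 3. The two rules side by side.**

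| Work done | Approximate time | Section 3.2 and Table 3 | Section 4.2 |
|---|---|---|---|
| Less than 60 min plus three sprints | Under 70 min | Excluded | Withdrawn from *this arm* |
| 60 min plus three to nine sprints | 70–83 min | Excluded | Continues |
| 60 min plus ten sprints | 84–85 min | Short of 90 min if read literally | Full protocol |

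The middle row is the direct conflict. Section 4.2 also lets the session end when cadence is lost, which blurs what completing it means.

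**Step 4. What lost pairs could cost.** First, the plan's own figure (Section 5.5: SD 95.4, control mean 299.3, 80% power, alpha 0.05, taken as two-sided). The difference is 0.30 × 299.3 = 89.8. With within-subject correlation 0, the SD of a paired difference is 95.4 × √2 = 134.9. A paired t-test then needs 19.7, so 20 pairs, and 20 / (1 − 0.20) = 25 recruited. Both planned numbers are reproduced. (The change of 134.7 printed in Section 5.5 is 45% of 299.3, not 30%, and does not reproduce 20. That is a separate matter.)

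The documents give no rate of failing the bout. The table assumes a range for the failing fraction f, on top of the 20% dropout:

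| f (assumed) | Pairs left, 25 × 0.8 × (1 − f) | Power, correlation 0 | Power, correlation 0.5 |
|---|---|---|---|
| 0% | 20 | 0.81 | 0.98 |
| 10% | 18 | 0.76 | 0.96 |
| 20% | 16 | 0.70 | 0.94 |

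If the 20% dropout allowance already covers these losses, the planned number does not change.

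**The case against.** The strongest case on the other side is that this is a within-subject comparison with a mechanistic hypothesis. Everyone is scheduled for the bout, and those retained act as their own controls. An effect in people who reached at least partial glycogen depletion is a sensible quantity. On this view, 90 min is a rounded label, Section 4.2 supplies the working rule, and analysis sets belong in an analysis plan that is not shown.

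Much of that stands. The lost participants do not create the arm imbalance of a parallel trial, and the absence of a named analysis set is not a finding. But the label argument does not remove the conflict. Section 4.2 itself treats the person who stops at three sprints as someone who could not complete the full protocol, which is what Section 3.2 and Table 3 exclude. Nor does it make the criterion assessable before randomisation.

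A reader might infer three stronger conclusions, and the documents support none of them:

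- **That the exercise effect is inflated.** If a fraction f fails and gains nothing from the exercise, the effect in those retained exceeds the overall effect by 1/(1 − f): 1.11 at 10% and 1.25 at 20%. Both inputs are assumptions, and zero gain is extreme for someone who stops just short of the minimum. Removal depends on cycling performance, not on autophagic flux.
- **That the sequences become unbalanced.** With equal failure rates, both sequences lose the same expected number of pairs. What differs is whether an unpaired A period remains. If *this arm* means Intervention B only, a Group 2 participant could still provide one in phase 2.
- **That Intervention A data are discarded.** That would follow from a complete-case repeated-measures ANOVA. Section 5.6 also permits a linear mixed model, which keeps unpaired periods, and nowhere says that withdrawn participants' data are dropped.

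**Conclusion.** The point holds as a fault in stated rules. An eligibility criterion rests on something observed only after randomisation and only under Intervention B. It conflicts with Section 4.2 for anyone who stops between about 70 and 83 min. The withdrawal wording is unclear in a crossover and sits badly with the statement in Section 3.1 that all participants complete both interventions.

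The consequences are a contrast restricted to people who tolerate the bout, missing data whose timing differs by sequence, and fewer pairs. The direction and size of any bias cannot be determined from the documents. The power loss ranges from negligible to about 11 percentage points (0.81 to 0.70). The upper end assumes 20% bout failure beyond the dropout allowance and zero within-subject correlation. The matter is mainly one of interpretability. It should be settled before data accrue, because samples not taken after a withdrawal cannot be recovered.

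**What to change.** 1. Reconcile Section 3.2, Table 3 and Section 4.2 so that eligibility uses only what can be assessed before randomisation and one completion rule applies throughout. Which completion rule is for the sponsor to decide.
2. State whether *this arm* means the Intervention B period or the whole trial, and align Section 3.1 with the answer.
3. Leave the safety stopping rules as they are.
4. Keep collecting outcome samples from randomised participants who continue the fast, whatever part of the bout they completed.
5. Make the analysis by assigned intervention primary, with a model that keeps unpaired periods, such as the mixed model that Section 5.6 already permits. Use the completion rule only to define a supplementary per-protocol set.

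The cost is wording in four places (Sections 3.1, 3.2 and 4.2, and Table 3), a line in the analysis section, and a few further samples. The downside is slight dilution of the primary estimate by incomplete exercisers; the per-protocol analysis would show the result without them.
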